## Abstract

**Background:**

Attention-deficit/hyperactivity disorder (ADHD) is a common neurodevelopmental disorder associated with numerous functional deficits and poor long-term outcomes. Internationally, behavioral interventions are recommended as part of a multimodal treatment approach for children with ADHD. Currently, in Japan, there are limited interventions available to target ADHD. Well Parent Japan (WPJ), a new hybrid parent-training program, provides a culturally acceptable and effective way to help support Japanese children with ADHD and their parents.

**Objective:**

This pragmatic multicenter randomized controlled trial aims to provide preliminary evidence about the effectiveness and cost-effectiveness of WPJ evaluated against treatment as usual (TAU) within routine Japanese mental health services.

**Methods:**

Mothers of children (aged 6-12 years) diagnosed with ADHD were recruited from child and adolescent mental health care services at three hospital sites across Japan (Fukui, Fukuoka, and Okinawa). The mothers were randomized to receive immediate treatment or TAU. The effectiveness and cost-effectiveness of WPJ over TAU at the end of the intervention and at 3-month follow-up will be evaluated. The primary outcome is maternal parent domain stress in the parenting role. The following secondary outcomes will be explored: child behavior, including severity of ADHD symptoms; parenting practices; emotional well-being; and the parent-child relationship and maternal child domain parenting stress. Data analysis will follow intention-to-treat principles with treatment effects quantified through analysis of covariance using multilevel modeling. An incremental cost-effectiveness ratio will be used to analyze the cost-effectiveness of the WPJ intervention.

**Results:**

Study funding was secured through a proof-of-concept grant in July 2018. Approval by the institutional review board for the data collection sites was obtained between 2017 and 2019. Data collection began in August 2019 and was completed in April 2022. Participant recruitment (N=124) was completed in May 2021. Effectiveness and cost-effectiveness analyses are expected to be completed by July 2022 and December 2022, respectively. These timelines are subject to change owing to the COVID-19 pandemic.

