### Sample Size Calculation

Parent domain parenting stress score at week 14 is the primary outcome measure and informed our sample size calculation. On the basis of the results of our pilot RCT [22], to detect a 0.5 standardized effect size at week 14 using 80% power at a 2-tailed .005 significance level, assuming the correlation between the baseline and follow-up measures is 0.35, 112 participants were required. After adjusting for a 15% attrition rate, the target sample size was inflated to 132.

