### Limitations

In recruiting through hospital clinics, the study does not include self-referred families in the community, possibly reducing the generalizability of the findings. Having clinic doctors (in Japan, the diagnosis of ADHD is limited to medical doctors; thus, referrals to the research were made by those responsible for the diagnosis of ADHD in the children) identify eligible families may have resulted in the referral of those dealing with more severe or comorbid ADHD, or mothers deemed most in need or most likely to benefit from participation in WPJ. Nonetheless, this is consistent with the aim of the research; that is, to evaluate WPJ within the Japanese child and adolescent mental health care system with a view toward future implementation of the intervention within this system. As a pragmatic trial, study site differences will be evaluated; however, we do not control for the effects of group leader skills on treatment outcomes. All group leaders are provided with the same training and are supervised by SS, which should help minimize differences in program delivery. The registration of the protocol was retrospective, and participant recruitment is now complete. No changes were made in the study protocol.

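### Recruitment closed at 124 against a target of 132, and the article does not compare the two or give the consequence (about 105 evaluable and 78% power at two-sided .05 under the plan's own attrition)

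*Protocol article*

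**What the plan says.** The Sample Size Calculation section sizes the trial on the week 14 parent domain stress score, for an effect of half a standard deviation and power of 80%. The level of the test is printed as follows: "at a 2-tailed .005 significance level". The evaluable number comes with its correlation assumption: "assuming the correlation between the baseline and follow-up measures is 0.35, 112 participants were required". The enrolment target then makes an allowance for dropout: "After adjusting for a 15% attrition rate, the target sample size was inflated to 132".

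The Results paragraph of the Abstract gives the achieved number: "Participant recruitment (N=124) was completed in May 2021".

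The Results section gives recruitment dates and describes the COVID-19 postponement and suspensions, but no comparison with the target. The Discussion says that stigma, unfamiliarity with group interventions and the pandemic made recruitment harder, but not that the target was missed. Limitations ends: "participant recruitment is now complete. No changes were made in the study protocol".

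**The concern.** The article prints both the number the plan needed to enrol and the smaller number it did enrol, and leaves them unconnected. The only power statement a reader meets is the planning figure of 80%, which depends on enrolling 132. When the article was written recruitment had closed and the analyses were still pending, so the shortfall was already known. A null or borderline primary result would be read against a planned size that was not reached, unless the reader noticed the gap and did the sum.

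This does not depend on an analysis plan or fuller protocol that is not shown. Both numbers are in the article itself.

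**Working it through.** **Inputs.** From Sample Size Calculation: effect 0.5 SD, power 80%, two-tailed level printed as .005, baseline to follow-up correlation 0.35, 112 required, 15% attrition, target 132. From the Abstract: 124 recruited. The allocation ratio is not stated; 1:1 is assumed.

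**Step 1: reproduce the plan's figure.** For a baseline-adjusted comparison of two means, the residual variance is 1 − 0.35² = 0.8775, and

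n per arm = 2 × (z for the level + z for power)² × 0.8775 / 0.5².

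- At two-sided .05: 2 × (1.960 + 0.842)² × 0.8775 / 0.25 = 55.1, rounded up to 56, total **112**. Then 112 / 0.85 = 131.8, rounded up to **132**. Both printed figures are reproduced.
- At two-sided .005, as printed: 2 × (2.807 + 0.842)² × 0.8775 / 0.25 = 93.5, rounded up to 94, total **188**. Then 188 / 0.85 = 221.2, rounded up to **222**. Neither printed figure is reproduced.

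The consequence of the shortfall is therefore worked at .05, with the .005 result shown beside it.

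**Step 2: the shortfall.** 132 − 124 = 8, and 8 / 132 = 6.1%. At the assumed attrition, 124 × 0.85 = 105.4 evaluable, against 112.

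**Step 3: power.** With N evaluable in total, SE = √(4 × 0.8775 / N), and power = Φ(0.5 / SE − critical value).

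- N = 105.4: SE = 0.1825, and 0.5 / 0.1825 = 2.740. At .05, Φ(2.740 − 1.960) = Φ(0.780) = 78.2%.
- N = 112: SE = 0.1770, and 0.5 / 0.1770 = 2.824. At .05, Φ(2.824 − 1.960) = Φ(0.864) = 80.6%.

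| Attrition among 124 | Evaluable | Power at .05, normal | Power at .05, noncentral t | Power at .005, normal |
|---|---|---|---|---|
| 0% | 124 | 84.4% | 83.9% | 56.6% |
| 9.7% | 112 | 80.6% | 79.9% | 50.7% |
| 15% (plan) | 105.4 | 78.2% | 77.5% | 47.3% |

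**Step 4: detectable effect with 80% power at .05.** (1.960 + 0.842) × SE gives 0.496 SD at 112 and 0.511 SD at 105.4.

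**Step 5: attrition at which 112 is still reached.** 1 − 112 / 124 = 9.7%.

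**The case against.** The strongest reply is that this is minor and nothing is hidden. The target and the achieved number are both printed, and the Discussion names the obstacles to recruitment. The loss is about 2.5 percentage points of power, and it is conditional: attrition is not reported, and at 9.7% or less the 112 is met. The 105 is also a complete-case count, whereas Effectiveness Analyses plans an intention-to-treat analysis with multiple imputation in a multilevel model, which may recover some precision. All of this stands as a limit on the size of the point. It does not remove it, because the plan itself sized the trial by discounting for attrition; measured the same way, 124 falls short. There was also almost no margin, since by the noncentral t 112 gives 79.9%.

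Three stronger readings are tempting, and the article does not support them.

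- A reader might infer that the closing statement in Limitations is false. It says that the protocol was not changed. Missing a recruitment target is an outcome of conduct, not a protocol change, so the two do not conflict.
- A reader might infer that the article claims 80% power for the 124 recruited. It does not. The 80% is a prospective planning figure, and a planning calculation is not normally rewritten once recruitment has closed.
- A reader might lower the power further for clustering within therapy groups. The article gives neither an intraclass correlation nor a therapy-group size, so any such figure would rest on outside assumptions. That is a separate question from the shortfall.

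**Conclusion.** The point holds as a gap in reporting with a modest consequence. Enrolment closed 8 below the stated target and the article does not say what that means. Under the plan's own 15% attrition about 105 mothers would be evaluable. Power for 0.5 SD is then about 78% (77.5% by the noncentral t), against the planned 80%, and the effect detectable with 80% power is about 0.51 SD.

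These figures rest on three assumptions: 1:1 allocation, a two-sided level of .05, and a complete-case count at the assumed attrition. The second matters most. The article prints .005, and the choice of level moves power at 105 evaluable between about 78% and about 47%, far more than the shortfall does. No achieved-power figure can be quoted sensibly until the level is settled.

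**What to change.** 1. Reconcile the printed .005 with the 112 and 132 beside it. With the other stated inputs, .05 gives both figures exactly and .005 would need 188 evaluable and 222 enrolled. If .05 was intended, correct the level; if .005 was intended, the sample size needs restating. Quoting power at .05 beside an unexplained .005 would add a new inconsistency.
2. Keep the calculation in Sample Size Calculation, identified as the planning figure.
3. If the level is confirmed as .05, add a sentence such as: *Recruitment closed at 124 of the planned 132; at the assumed 15% attrition about 105 would be evaluable, giving about 78% power at a two-sided .05 level.*
4. Note the shortfall in Limitations. Leave the statement that the protocol was not changed in place, since it remains true. Do not add power figures based on assumed intraclass correlations.

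If .05 is confirmed, the cost is one corrected number and about two sentences. The shortfall itself calls for no further enrolment and no change to the analysis.

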**Conclusions:**

This is the first multisite pragmatic trial of WPJ based on the recruitment of children referred directly to routine clinical services in Japan. This multisite randomized trial tests the effectiveness of WPJ in children and families by comparing WPJ directly with the usual clinical care offered for children diagnosed with ADHD in Japan. We also seek to assess and compare the cost-effectiveness of WPJ with TAU in Japan.

**Trial Registration:**

International Standard Randomised Controlled Trial Number ISRCTN66978270; https://www.isrctn.com/ISRCTN66978270

**International Registered Report Identifier (IRRID):**

DERR1-10.2196/32693

## Introduction

### Background

Attention-deficit/hyperactivity disorder (ADHD) is a common neurodevelopmental disorder with an estimated worldwide prevalence of approximately 5% [1]. In Japan, the prevalence estimates range from 2.5% [2] to 10% [3]. The disorder is associated with numerous functional impairments and poor long-term outcomes [4,5] and negatively affects parents’ emotional well-being, parenting practices, and the parent-child relationship [6]. Effective interventions for children with ADHD and their families are therefore a high priority [7].

Current clinical guidelines recommend a multimodal treatment approach for ADHD that incorporates both pharmacological and nonpharmacological treatment options [8-10]. Parenting interventions are an example of a recommended nonpharmacological treatment option with proven efficacy in numerous clinical trials [11,12]. Recommended interventions generally provide parents with behavioral strategies aimed at increasing the frequency of appropriate behavior while reducing the frequency of unwanted behavior in children. The needs of families of children with ADHD have received less attention, with only a few studies directly targeting parental well-being [13,14].

### Behavioral Interventions for ADHD in Japan

Parent-training interventions are becoming more widely accepted in Japan with increased implementation, especially in community settings. Although efforts have been made to develop programs to address the needs of families of children with a range of neurodevelopmental disorders [15], the availability of interventions specifically designed for ADHD remains limited.

To our knowledge, none of the behavior programs currently being implemented in Japan includes specific elements to address parental coping or emotional well-being. In addition, nothing is known about the cost-effectiveness of behavioral interventions for ADHD in Japan.

### Development of Well Parent Japan

For Japanese families, the 8-session group-based New Forest Parenting Programme (NFPP) has been front-loaded with 5 additional sessions designed to increase mother’s understanding of ADHD and to address their psychological well-being and readiness to complete the NFPP program. These sessions were added on the recommendation of participants in our pilot and proof-of-concept studies [16] to provide additional support for mothers. Culturally, Japanese mothers are held responsible for their child’s behavior and struggle to request support for themselves and their children. These 5 sessions included auxiliary psychoeducation about ADHD and culturally tailored stress management training, cognitive restructuring, strategies for effective communication, and problem-solving skills, adapted from the 9-week parent stress management program [14].

The NFPP has been specifically developed for the treatment of ADHD. In addition to behavioral strategies to manage oppositional and defiant behavior, it includes games and activities targeting purported neuropsychological deficits underlying some of the symptoms of ADHD [17], designed to enhance the child’s cognition and self-regulation [18]. Numerous randomized controlled trials (RCTs) have shown that the receipt of NFPP is associated with a reduction in ADHD symptoms and improvements in parental well-being [18-21]. With the support of the program developers, the NFPP sessions were specifically adapted for use with Japanese families [16].

A recent pilot RCT of Well Parent Japan (WPJ) [22] demonstrated that participation in the program was associated with several positive outcomes compared with the wait-list control group; that is, significant reductions in parenting stress, higher levels of parenting self-esteem and use of more effective parenting strategies, reduced child aggression, internalizing problems, and a trend toward reduced inattention. Mothers who participated in WPJ also responded less negatively toward their children. WPJ appears to be an efficacious psychosocial intervention for ADHD in Japan, with the group format and the session content well tolerated.

### Objectives

This study aims to extend the results from the pilot RCT [22] to a larger multicenter pragmatic trial to assess the effectiveness and cost-effectiveness of WPJ compared with treatment as usual (TAU) in child and adolescent mental health care services in Japanese hospitals. WPJ will be compared against TAU at the end of the intervention and again after 3 months (short-term follow-up).

The primary objective is to compare the effectiveness of WPJ against TAU on maternal parent domain parenting stress, that is perceived stress in the parent-child dyad arising from characteristics of the parent, measured with the Parent Stress Index [23,24]. Parent domain stress was selected as the primary outcome measure given WPJ’s strong focus on the emotional well-being of participating mothers. Secondary objectives include comparison of the effectiveness of WPJ against TAU in improving child behavior, parental well-being, and parenting practices and to explore the cost-effectiveness of WPJ.

## Methods

### Study Design

A multisite pragmatic RCT comparing the effectiveness and cost-effectiveness of WPJ (treatment arm) with TAU (control arm). Both arms will be tested at baseline, immediately after the intervention arm completes WPJ at week 14, and at 3 months follow-up; that is, week 26. The study is being carried out through Japanese child and adolescent mental health care services at three different hospital sites in Japan (Fukui, Fukuoka, and Okinawa). Table 1 lists the schedule of parent self-report, teacher, and objective assessments at each time point, whereas Figure 1 summarizes the study design and flow of participants through the trial.

**Table 1 table1:** Standard Protocol Items: Recommendations for Interventional Trials schedule.

Time point			Screening	Baseline	Intervention	Posttreatment (week 14)	3-month follow-up (week 26)
**Enrollment**							
	Informed consent		✓				
	Informed assent-child			✓			
**Randomization**							
	Well Parent Japan				✓		
	TAU^a^						
**Assessments**							
	**Diagnostic measures**						
		AQ^b^-child		✓			
		CAARS^c^-adult		✓			
	**Child behavior rating scales—Mother**						
		SNAP^d^ parent		✓		✓	✓
		Vanderbilt-Parent		✓		✓	✓
		Impairment Rating Scale		✓		✓	✓
	**Child behavior rating scales—Teacher**						
		SNAP teacher		✓		✓	✓
		Vanderbilt-teacher		✓		✓	✓
	**Mother self-report scales**						
		PSI^e^		✓		✓	✓
		Parenting scale		✓		✓	✓
		PSOC^f^		✓		✓	✓
		PLOC^g^		✓		✓	✓
		Family strain		✓		✓	✓
		BDI-2^h^		✓		✓	✓
	**Mother-child interaction measures**						
		SCIFF^i^ and SCIPD^j^		✓		✓	
		R-FMSS^k^		✓		✓	
	**Cost-effectiveness interview**						
		JHEC^l^		✓		✓	✓

^a^TAU: treatment as usual.

^b^AQ: Autism Quotient.

^c^CAARS: Conners Adult ADHD Rating Scales.

^d^SNAP: Swanson, Nolan, and Pelham Scale.

^e^PSI: Parenting Stress Index.

^f^PSOC: Parenting Sense of Competence.

^g^PLOC: Parental Locus of Control.

^h^BDI-2: Beck Depression Inventory-2.

^i^SCIFF: System for Coding Interactions and Family Functioning.

^j^SCIPD: System for Coding Interactions in Parent-Child Dyads.

^k^R-FMSS: Revised Five-Minute Speech Sample.

^l^JHEC: Japanese Health Economic Cost.

**Figure 1 figure1:**
[figure not shown]
Study design and participant flow. R-FMSS: revised Five-Minute Speech Sample; RA: research administrator; TAU: treatment as usual; WPJ: Well Parent Japan.

### Trial Registration

The study was retrospectively registered with the International Standard Randomised Controlled Trial Number after the first of 3 waves of participant recruitment (trial registration number: ISRCTN66978270). Registration delay was an unintended consequence of ill health of one of the principal investigators, which disrupted study preparation. This oversight was identified after the first wave of participant recruitment and the trial was subsequently registered. Ethical approval for the trial, as described in the protocol, was obtained at all intervention sites before participant recruitment.

### Sample Size Calculation

Parent domain parenting stress score at week 14 is the primary outcome measure and informed our sample size calculation. On the basis of the results of our pilot RCT [22], to detect a 0.5 standardized effect size at week 14 using 80% power at a 2-tailed .005 significance level, assuming the correlation between the baseline and follow-up measures is 0.35, 112 participants were required. After adjusting for a 15% attrition rate, the target sample size was inflated to 132.

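### The printed two-sided .005 level does not give 112 participants; .05 does, and at .005 a sample of 112 has about 51% power rather than 80%

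*Protocol article*

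**What the plan says.** The Sample Size Calculation section of the protocol article gives the whole calculation in a few lines. The endpoint is fixed at one time point: "Parent domain parenting stress score at week 14 is the primary outcome measure". The target is "to detect a 0.5 standardized effect size at week 14", and the remaining inputs and the result are "80% power at a 2-tailed .005 significance level, assuming the correlation between the baseline and follow-up measures is 0.35, 112 participants were required". The section then adds: "After adjusting for a 15% attrition rate, the target sample size was inflated to 132".

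The Effectiveness Analyses section plans a baseline-adjusted analysis of covariance in a multilevel model, so the correlation of 0.35 enters as the usual variance reduction. That section names no significance level. No passage gives a reason, such as a multiplicity adjustment, for a level stricter than the conventional one. The Abstract reports that 124 participants were recruited.

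**The concern.** A two-sided level of .005 is ten times stricter than the conventional .05 and needs a much larger sample for the same effect and power. A total of 112 looks too small for it and is close to what one would expect at .05.

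The level matters because it is the only one printed for a test of the primary outcome. If it is taken at face value, the trial has roughly an even chance of detecting the effect it was designed for. If the analysis uses .05 while the published text still says .005, a week-14 p-value between the two would count as positive under one and negative under the other. Recruitment and data collection are reported as complete, and registration was retrospective. A threshold settled only after the results are known would be hard to defend, even if it had always been .05.

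**Working it through.** **Inputs.** From Sample Size Calculation: standardized effect d = 0.5, power 80%, two-sided α = .005, baseline to follow-up correlation r = 0.35, N = 112 before attrition, attrition 15%, inflated N = 132. From the Abstract: 124 recruited. The allocation ratio is not stated; I assume 1:1. Unequal allocation would only raise the required total.

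**Formula.** For a baseline-adjusted comparison at one follow-up:

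n per arm = 2 (z₁₋α/₂ + z₀.₈₀)² (1 − r²) / d²

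Here 1 − r² = 1 − 0.1225 = 0.8775, so n = 7.02 × (z₁₋α/₂ + 0.8416)².

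**The plan's figures, reproduced at α = .05.** (1.9600 + 0.8416)² = 7.849, and 7.02 × 7.849 = 55.1. That is 56 per arm, 112 in total. 112 / 0.85 = 131.8, so 132. Both published numbers match.

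**The same calculation at the printed α = .005.** (2.8070 + 0.8416)² = 13.313, and 7.02 × 13.313 = 93.5. That is 94 per arm, 188 in total. 188 / 0.85 = 221.2, so 222.

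**Power.** With 56 per arm, the expected test statistic is 0.5 / (√0.8775 × √(2/56)) = 2.824. At .005, power = Φ(2.824 − 2.807) = 50.7%. At .05, power = Φ(2.824 − 1.960) = 80.6%. For other analysed totals:

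| Analysed | Power at .005 | Power at .05 |
|---|---|---|
| 105 (124 less 15%) | 47.1% | 78.1% |
| 112 | 50.7% | 80.6% |
| 124 | 56.5% | 84.4% |
| 132 | 60.2% | 86.6% |

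At .005 with 112 analysed, the effect detectable with 80% power is (2.8070 + 0.8416) × √0.8775 × √(2/56) = 0.65 SD.

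**Working backwards from 112.** With the other inputs as printed, 112 participants and 80% power imply a two-sided level of 0.047. To keep .005, the correlation would have to be about 0.69 instead of 0.35.

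**Other readings at .005.** Total N required:

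- One-sided test, baseline-adjusted: 164
- Follow-up score only, no baseline adjustment: 214
- Change score: 278
- Noncentral t instead of the normal approximation: 192
- Mean of the two follow-ups, baseline-adjusted, with a correlation of 0.35 assumed between follow-ups: 118

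The last comes nearest. It would reach 112 if the correlation ρ between follow-ups were just under 0.30: the variance factor (1 + ρ)/2 − 0.1225 must equal 56 / (2 × 13.313 / 0.25) = 0.526, so ρ = 0.297. The article states no such correlation, and the calculation is expressly for week 14 alone, so this reading does not fit the text.

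The noncentral t at .05 gives 114 (79.9% power at 112), so the published 112 is the normal-approximation result.

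**The case against.** The strongest reply is that this is one superfluous zero. If .05 was the planning level, the trial was sized correctly, correcting the print loosens nothing, and the 51% describes a test nobody meant to run. Further, the .005 appears as an input to a sample size calculation and not as a declared decision rule. The Effectiveness Analyses section speaks of estimates and their precision and defers detail to a separate analysis plan, which may state .05. The 105-participant case also treats dropouts as contributing nothing, whereas multiple imputation and a multilevel model are planned.

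Much of this stands. The misprint is the likelier reading, and the 51% holds only if .005 is applied. Nothing in the article shows that anyone changed a threshold. At .05, recruiting 124 instead of 132 costs little: 78% power at 105 analysed, 84% at 124. Imputation would recover some information, though not all of it.

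None of it makes the printed figures consistent. The absence of a level from the article's analysis section is not the complaint; the complaint is that the level the article does print is incompatible with its own power and sample size. An analysis plan using .05 would contradict the published text until that text is corrected.

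**Conclusion.** The concern holds. With an effect of 0.5, a correlation of 0.35 and 80% power, 112 participants follow from two-sided .05 and not from .005. The printed level would need 188 analysed and 222 recruited, 76 and 90 more than published. If .005 is the real level, power at 112 analysed is about 51%, and about 47% to 57% over 105 to 124 analysed. If .05 is the real level, the planned size is adequate and only the printed figure is wrong.

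The exact match to both 112 and 132 strongly favours .05, but the article cannot settle it. The figures assume 1:1 allocation, the normal approximation and one baseline-adjusted comparison at week 14. The noncentral t lowers the 51% slightly, to 48.7%.

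**What to change.** Before the data are locked, the authors should check the original calculation and state which level applies to the primary week-14 comparison.

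- **If .05:** correct the Sample Size Calculation section to two-sided .05, leave 112 and 132 unchanged, and state .05 for the primary test in the statistical analysis section and the analysis plan.
- **If .005:** keep it, give the reason for it, and restate the power as about 51% with 112 analysed, noting that 80% power would have needed 188 analysed.

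Either way the cost is one corrected figure and a sentence confirming the level, repeated in the analysis plan and the registry entry if they carry the same number. Neither was available to check. Sample size, arms, endpoint and model stay as they are.
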